### Handling missing data

Maximum likelihood estimation of mixed-effects models will be used to account for missing data. In the context of a mixed-effects model, this is equivalent to an assumption of data missing at random. We will conduct sensitivity analyses assessing this assumption including comparison of participants with and without missing values with respect to baseline and practice characteristics. If differential patterns emerge, we will consider the use of multiple imputation by chained equations and/or inverse probability weighting to adjust for missing data.

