### Overview of the hypertension program and implementation strategy

Two key components define our protocol: a hypertension management program and an external support system for nurses. A nurse-led (TASSH) program will be implemented at all PHCs. TASSH includes identification of patients with hypertension, treatment of patients with uncontrolled hypertension using antihypertensive medication based on a standard treatment and drug titration protocol (see Supplemental file A), lifestyle counseling, and referral to physicians for complicated cases of hypertension (i.e., nonresponsive to first-line treatment after maximum doses, *BP* ≥ 180/110 mm Hg, or with comorbid diabetes mellitus, heart attack, stroke, kidney disease, or heart failure, or pregnancy following study enrollment) [17]. With the exception of TASSH focusing on nurses providing hypertension care, these components of TASSH are similar to the Nigerian Hypertension Treatment Protocol. The experimental implementation component, PF, is an approach to service integration that will be introduced to all PHCs in a stepwise manner over the duration of the trial. PF involves provision of external expertise on practice redesign and a tailored approach to evidence-based care [18–22]. It includes both a role (practice facilitator) and a process for supporting primary care practices to build motivation and capacity at the systems and individual levels to improve organizational performance [19, 21–24]. Practice facilitators (typically nurses) are trained to work with primary care practices to develop the necessary skills to adapt evidence-based strategies, e.g., task shifting/sharing, to their practice environment [25]. In this study, the practice facilitators are nurses with an average of 35 years in clinical practice.

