### Primary outcome

Adoption (i.e., uptake) is the utilization of components of TASSH. TASSH adoption will be defined as nurses showing utilization of all of the following components: (1) identifying PLWH with uncontrolled hypertension, (2) measuring PLWH’s anthropometrics and BP with a valid automated device following standard procedures, (3) initiating lifestyle counseling and medication treatment every 1–3 months, and (4) referring PLWH with severely elevated BP and complicated hypertension to physicians for further care. Adoption will be measured at the clinic level, in aggregate, each month from the baseline period of the first cohort through the end of follow-up, for all those PLWH with BP screens by case managers or those previously diagnosed with hypertension at a prior visit by the nurses. Table 1 expands on the specific measures of adoption.

**Table 1 Tab1:** Measurement of adoption

Outcome	Components	Data sources	Measurement
**Adoption**	**Identifying PLWH with uncontrolled hypertension**		
	• Measuring blood pressure • Measuring anthropometrics • Assessing comorbidities • Asking about lifestyle factors (physical activity, alcohol consumption, tobacco use, and diet)	Blood pressure monitoring register Hypertension treatment card	Proportion of PLWH who receive all applicable components of the protocol at each PHC during each time period
	**Counseling PLWH on lifestyle factors**		Adoption will be measured each month at each clinic utilizing aggregate data
	**Treating and referring** • Initiating treatment under the Nigeria hypertension protocol • Titrating drugs under the Nigeria hypertension protocol • Referring PLWH with complicated hypertension to secondary health center (as needed)		

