## Statistical approach

### Power and sample size justification

As the level of randomization for this SW-CRT is at the practice level, there are several important study design features: *K*, the number of primary care practices, and *m*, the average number of PLWH recruited per practice, as well as the relatedness of individuals within sites (when individual level data are utilized for analysis). Specifically, the *m* participants will be nested (grouped) within the *K* practices. This nesting will lead to additional dependency in outcomes of participants within a practice; the degree of this dependency, the intraclass correlation coefficient (ICC), will contribute to the necessary increase in sample size to maintain the same level of power as would result if the unit of randomization was independent individual participants rather than participants within practices. Prior studies examining the effects of TASSH on BP control have demonstrated improvements in BP control level ranging from 20 to 25% over usual care. We expect a somewhat smaller effect, as we are testing the effect of PF plus TASSH on BP control.

Trials targeting BP control have found ICCs for BP control ranging between 0.02 and 0.06. In addition, preliminary evidence from our UG3 pilot phase suggests that ICC estimates for BP control under UC align with these estimates. Adoption will be measured as outlined above through aggregate data at the site level each month. It is expected that TASSH adoption will be lower than 50% before PF. We expect the estimates in Table 2 to be conservative if the baseline proportion for adoption is less than 40%. We will test our primary and secondary hypotheses at the 5% two-sided type 1 error level. For secondary measures that will utilize individual level data, we expect to enroll 28–32 individuals on average, expecting approximately 10% attrition over the course of the study period, resulting in at least 25 on average per site.

**Table 2 Tab2:** Achieved power for differences in outcomes ranging from 15 to 20%

ICC	At baseline (no PF): 50%		At baseline (no PF): 40%	
	**Difference: 15%** **Odds ratio: 1.9**	**Difference: 20%** **Odds ratio: 2.3**	**Difference: 15%** **Odds ratio: 1.8**	**Difference: 20%** **Odds ratio: 2.2**
**0.01**	**82%**	**97%**	**84%**	**98%**
**0.03**	**79%**	**96%**	**80%**	**96%**
**0.05**	**77%**	**95%**	**78%**	**96%**

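### The named check on missing at random cannot assess that assumption, and the conditional fallback methods assume it again (BP control, secondary outcome)

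*Protocol article*

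**What the plan says.** The section Handling missing data of the protocol article has three steps.

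- Main approach: "Maximum likelihood estimation of mixed-effects models will be used to account for missing data". The article adds that "this is equivalent to an assumption of data missing at random".
- Check: "We will conduct sensitivity analyses assessing this assumption including comparison of participants with and without missing values with respect to baseline and practice characteristics".
- Fallback, only if that comparison shows differences: "we will consider the use of multiple imputation by chained equations and/or inverse probability weighting to adjust for missing data".

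The section Sensitivity analysis deals with the active stepped-wedge period and permutation tests and does not mention missing data.

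Two other places matter. The power section enrols 28 to 32 participants per site, "expecting approximately 10% attrition over the course of the study period". The overview of the hypertension program has nurses refer complicated cases to physicians. Those include patients who are "nonresponsive to first-line treatment after maximum doses", severe BP, several comorbidities, and pregnancy after enrolment. Table 1 counts this among the adoption components: "Referring PLWH with complicated hypertension to secondary health center (as needed").

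**The concern.** MAR is a statement about what missingness depends on once the observed data are taken into account. Comparing people with and without missing values on baseline and practice characteristics shows whether missingness is related to those characteristics. It can speak against missing completely at random. It cannot show whether, given the observed data, missingness also depends on the BP that was not recorded. The text nevertheless presents it as an assessment of MAR.

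The next step has the same limit. Chained-equation imputation and inverse probability weighting, as described, replace one MAR analysis with another. They are also considered only if a baseline difference is seen, although harmful missingness need not leave one.

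At stake is the reading of the BP control result. If those without a reading are more often uncontrolled than the model predicts, the likelihood analysis, imputation and weighting can agree and share the same error. BP control also enters the fidelity analysis. Adoption, the primary outcome, comes from monthly aggregate clinic data and is not touched by this.

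**Working it through.** **1. The plan's own figure.** Table 2 uses 25 per site after 10% attrition from 28. Check: 28 × 0.90 = 25.2, and 25 / 0.90 = 27.8, rounded up to 28. The figure reproduces. About 3 of 28 participants per site are lost. The article gives no split by condition.

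**2. Can the named steps detect or repair outcome-dependent missingness?** Illustrative simulation: 400,000 records, one standardised baseline variable, binary BP control, about 10% missing. All settings are assumptions.

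| Mechanism | Baseline difference, missing vs observed | True control | Complete cases | Weighting | Imputation |
|---|---|---|---|---|---|
| Missing depends on baseline only (MAR) | 0.49 SD | 62.9% | 63.7% | 62.9% | 62.9% |
| Missing depends on the unseen outcome (20% of uncontrolled, 3.5% of controlled); baseline predicts outcome | 0.31 SD | 62.9% | 67.2% | 66.7% | 66.7% |
| Missing depends on the unseen outcome (20% and 4.6%); baseline unrelated to outcome | -0.01 SD | 65.0% | 68.9% | 68.9% | 68.9% |

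The first two rows both show a baseline difference. Weighting and imputation repair the first, and both leave the second about 3.8 points too high. In the third row the comparison shows nothing, so the fallback would not be triggered, and every estimate is about 3.9 points too high. By hand for the third row: 0.65 × 0.954 / (0.65 × 0.954 + 0.35 × 0.80) = 0.6201 / 0.9001 = 68.9%.

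**3. Possible size for the difference between conditions.** Let c be observed control, m the proportion missing, and k the control rate among the missing relative to the observed, the same in both conditions. Full-cohort control is c(1 - m) + k·c·m, so the overstatement of the difference is

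(1 - k) × (c_PF × m_PF - c_UC × m_UC).

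Observed control is assumed to be 65% vs 50% or 55% vs 40%, the 15-point scenarios of Table 2. The split of attrition and k are assumptions. No credit is given for earlier readings on the same person.

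| Missing under PF / usual care | 65 vs 50, k = 0 | 65 vs 50, k = 0.5 | 55 vs 40, k = 0 | 55 vs 40, k = 0.5 |
|---|---|---|---|---|
| 10% / 10% | +1.5 | +0.75 | +1.5 | +0.75 |
| 15% / 5% | +7.25 | +3.6 | +6.25 | +3.1 |
| 5% / 15% | -4.25 | -2.1 | -3.25 | -1.6 |

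Entries are percentage points; plus means that the PF effect is overstated. Example: 0.65 × 0.15 - 0.50 × 0.05 = 0.0975 - 0.025 = 0.0725. The sign turns when c_UC × m_UC exceeds c_PF × m_PF. That happens when usual-care loss is more than 0.65 / 0.50 = 1.30 times PF loss, or 0.55 / 0.40 = 1.375 times.

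The 1.5-point figure also needs the missing to be alike in both conditions. At equal 10% loss, if only the missing under PF were all uncontrolled and those under usual care matched the observed, it would be 0.65 × 0.10 = 6.5 points. Hence the departure should be varied by condition.

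**The case against.** The strongest reply has five parts.

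- **No analysis can test MAR from the observed data.** This is correct. The criticism is therefore not that a better test was missed. The text describes a step as assessing an assumption that it cannot assess, where an analysis of stated departures is what would inform.
- **This is a condensed article, the list of sensitivity analyses is open-ended, and the analysis plan is not shown.** This stands in part. It cannot be said that no departure analysis is planned. But the article does fix one check and one conditional fallback for this purpose, and those are fixed badly.
- **Referral does not mean lost BP data.** This stands. A reader might infer that the worst BP cases are referred out of the cohort, and more often under PF, so that the PF effect is inflated. The article does not say so. Severe BP is an exclusion only at baseline, and the BP procedure applies at each participant visit, including 12 months, with no exception for referral. Referral also covers comorbidity and pregnancy, which do not imply uncontrolled BP.
- **Referral after a recorded reading can be MAR.** This stands if that reading is in the imputation or weighting model, and the article does not limit those methods to baseline variables. The BP control model, however, uses only control status, so the recorded level above the threshold does not enter it.
- **The direction is open.** This stands. PF may raise referral, which is part of adoption, but it may also improve control and so reduce non-response.

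**Conclusion.** The point holds as a fault in the stated plan for one secondary outcome. The comparison on baseline and practice characteristics does not assess MAR, and the fallback methods stay within MAR. Agreement among them would be weak evidence of robustness.

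Referral of non-responding or severe cases is a plausible but undocumented route to BP-dependent missingness. The stronger conclusion, that the trial will overstate the PF effect on BP control, is not supported. It needs both loss of BP data after referral and greater loss under PF, and the article states neither. The shifts calculated above are illustrations that rest on an assumed split of the roughly 10% attrition and an assumed control rate among the missing; they are not estimates of bias. No figure in the article is wrong, and the analysis of adoption is unaffected.

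**What to change.** Keep the likelihood GLMM as the main analysis of BP control and change the sensitivity step.

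1. Describe the comparison of participants with and without missing values as descriptive only, and do not make any further analysis conditional on it.
2. Prespecify a delta-adjusted (tipping-point) multiple imputation for BP control. Vary delta separately for PF and usual care, in both directions. Include recorded systolic and diastolic BP and referral status as auxiliary variables. Report the delta at which the conclusion changes.
3. If wanted, show as one extreme bound an analysis that counts participants missing after referral for uncontrolled BP as uncontrolled. Do not apply it to those referred for comorbidity or pregnancy.

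The cost is a few sentences in the analysis plan and a little programming. No new data are needed, provided that referral and its reason are recorded for each enrolled participant; the article does not say whether they are. The downside is that the reported result may look less robust.

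If the full analysis plan already contains such an analysis, only the wording about assessing MAR needs correction.

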### Sensitivity analysis

While primary analyses will focus on estimation through GLMM and take all information gathered during the usual care and PF periods into account, we will also consider the evaluation of PF during the “active stepped wedge” phase, the period in which at least one block differs in terms of treatment group (those periods when all blocks are in usual care or PF are excluded). These evaluations will compare estimates of the GLMM method and those which estimate the treatment effect through robust nonparametric permutation methods. GLMMs require assumptions on the random effects, which if violated result in biased treatment effect estimates [46, 47]. The proposed permutation tests do not require these assumptions on the correlation structure but require that all clusters are not in the same treatment condition. We will assess the robustness of GLMM assumptions through the comparison of results from methods in this reduced set of observations.

## Discussion

For low-resource-high-need settings, overwhelmed by suboptimal healthcare systems and healthcare workforce shortage, context-specific approaches for integrating effective, evidence-based approaches are critically needed [16, 25]. Our study, MAP-IT, is one of few implementation science studies to include a health services’ strengthening implementation strategy approach to integrate hypertension management into HIV care and treatment in Akwa Ibom State, Nigeria, which has one of the highest HIV prevalence rates in the country. Specifically, the study is using an evidence-based task strengthening hypertension program and PF as the implementation strategy to enhance the adoption and sustainability of hypertension control and management among PLWH and their providers. Our PF strategy builds on current knowledge regarding how facilitation functions by the following: tailoring the hierarchical structure within PHCs to work with senior or retired nurses as facilitators focusing primarily on supporting HIV nurses to treat hypertension, enhancing clinic workflow by troubleshooting and goal setting with HIV nurses, and reinforcing the current hypertension treatment protocol in Nigeria as the standard of care for PLWH.

MAP-IT is one of the first studies to apply the i-PARiHS framework to the African context, as part of pre-implementation activities, to assess the capacity of healthcare facilities to deliver an evidence-based hypertension control program. The testing of TASSH among PLWH is also relevant given the recent implementation of the Nigerian Hypertension Treatment Protocol as the standard of care for treating individuals with hypertension at the primary care level. Previous studies demonstrate that primary care practices are more likely to adopt evidence-based standards of care through PF [18, 20, 22]. It is not clear, however, that this conclusion applies to PHCs in low- and middle-income countries (LMICs) experiencing a dual disease burden of chronic NCDs and HIV. MAP-IT will advance research and practice on the potential impact of PF as an implementation strategy to improve the adoption of hypertension standard of care for PLWH while providing health system-level improvements and outcomes in an LMIC setting.

More precisely, this study will provide evidence on the implications of engaging senior or retired healthcare workers as practice facilitators on the adoption and sustainability of an evidence-based hypertension control program for PLWH. In a country where these individuals are usually retired early at the age of 60 years or after 35 years of practice, adopting this strategy will help tap into their rich expertise. In short, our assessment of PF will provide key evidence on the impact of external facilitators on hypertension outcomes among PLWH and as a potential health services’ strengthening approach to support non-physician providers in LMICs experiencing a growing prevalence of comorbid HIV and hypertension.

## Limitations

Given the stepped wedge study design, there are methodological challenges to consider for this study. Despite the benefits of the stepped wedge design, a notable limitation is potential confounding due to temporal trends [28], wherein more clusters/PHCs are exposed to PF as the study progresses as opposed to the beginning. This scaffolding of PF will limit our ability to disentangle effects of time from the PF implementation strategy, i.e., the first PHCs/cohorts will be exposed to PF longer than later PHCs. To address this limitation, randomization of PHCs along with robust adjustment for temporal trends in modeling will be key.

## Implications

The results of our study will provide evidence for scaling up TASSH as a standard approach to reduce the burden of uncontrolled hypertension in PLWH. Furthermore, our understanding of PF as an effective strategy to improve the adoption of evidence-based practices in clinical settings remains incomplete because previous work has not examined PF in LMIC settings experiencing increased hypertension and HIV comorbidity. Lastly, the MAP-IT study is timely in its implementation, and the potential implications of the findings on strengthening integrated NCD-HIV care programs as PLWH are living longer and are increasingly at risk of having comorbid NCDs.

## Data Availability

Not applicable.

## Abbreviations

AKSACA: Akwa Ibom State Agency for Control of AIDS
BP: Blood pressure
CRT: Cluster randomized trial
CVD: Cardiovascular disease
DBP: Diastolic blood pressure
GLMM: Generalized linear mixed model
HIV: Human immunodeficiency virus
ICTR: Identifying, counseling, treating, and referring
FMOH: Federal Ministry of Health
i-PARiHS: Integrated Promoting Action on Research Implementation in Health Services
IRB: Institutional review board
LMICs: Low- and middle-income countries
MAP-IT: *Managing Hypertension * *Among* * People Living with HIV: an Integrated Model*
MOU: Memorandum of understanding
NACA: National Agency for the Control of AIDS
NCDs: Noncommunicable diseases
PF: Practice facilitation
PLWH: People living with HIV
PHCs: Primary healthcare centers
RE-AIM: Reach, effectiveness, adoption, implementation, and maintenance
SEM: Structural equation modeling
SBP: Systolic blood pressure
TASSH: Task-strengthening strategy for hypertension control
UNAIDS: Joint United Nations Programme on HIV/AIDS
WHO: World Health Organization
